#### **12.6.1.1 Diagnosis and Confidence**

- A difference between the Early Amyloid PET arm and the Late Amyloid PET arm in the time to communicate an etiologic diagnosis with a confidence  $\geq 90\%$  will be tested by the log-rank test. The cumulative incidence of diagnoses will be estimated with the Kaplan-Meier method.
- Changes in the managing physician's etiologic diagnosis at T3 vs T2 vs T1 in each arm
- The changes in the managing physician's diagnostic confidence at T3 vs T2 vs T1 vs T0, for participants in the Early Amyloid PET arm vs participants in the Late Amyloid PET arm
- The managing physician's estimate of the likelihood that the patient's symptoms are due to AD at T3 vs T2 vs T1 vs T0 in the Early Amyloid PET arm vs the Late Amyloid PET arm.
- Changes over calendar time in the placement of amyloid PET imaging in the patient workup for participants in the Free Choice arm. The Free Choice arm will be divided into 3 equal-sized groups, according to the date of randomisation. For the Free Choice arm, a change in the placement of amyloid PET imaging over time in the diagnostic workup will be tested by a log-rank test.

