##### **Diagnosis and Confidence**

- The difference between the Early Amyloid PET arm and the Late Amyloid PET arm in the time (from baseline) to communicate a very-high-confidence ( $\geq 90\%$ ) etiologic diagnosis to the patient.
- Change of etiologic diagnosis and incremental diagnostic confidence between Baseline visit (T0) and T1 in each arm.
- Changes in the managing physician's etiologic diagnosis at T3 vs T2 vs T1 in each arm.
- Changes in the managing physician's diagnostic confidence at T3 vs T2 vs T1 vs T0 in the Early Amyloid PET arm vs the Late Amyloid PET arm.
- The managing physician's estimate of the likelihood that the patient's symptoms are due to AD at T3 vs T2 vs T1 vs T0 in the Early Amyloid PET arm vs the Late Amyloid PET arm.
- Changes over calendar time in the placement of amyloid PET imaging in the patient workup for participants in the Free Choice arm.

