### 5.2 Research Hypothesis

The early adoption of A $\beta$  PET imaging with [ $^{18}$ F]florbetaben or [ $^{18}$ F]flutemetamol will enable an earlier etiologic diagnosis with high confidence vs the late adoption of A $\beta$  PET imaging with [ $^{18}$ F]florbetaben or [ $^{18}$ F]flutemetamol when used in patients with a cognitive impairment possibly due to AD, specifically in patients with SCD Plus, MCI, or dementia.

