In all Arms, between Baseline visit and Week 12 visit, each time a biomarker is available, the result must be communicated to the managing physician, and the etiological diagnosis as well as the diagnostic confidence must be collected immediately. This will provide a sequential collection of diagnosis and diagnostic confidence up to Week 12 visit.

Amyloid load will be defined on the basis of visual reads at all time points. Only for the secondary aim of the disease modelling, amyloid load will be defined quantitatively. The results of the optional second amyloid PET scans (early amyloid PET arm) will be provided to the managing physician and may be used for clinical purposes.

The goal will be to enrol 100 participants per stratum in each arm, for a total of 900 participants.

Sites will be using PET-CT or PET-MR depending on what technology is available at each site.

Participation in the study will not prevent participants from having any currently available diagnostic investigation, but rather will give participants the opportunity to have access to amyloid PET imaging, a diagnostic test approved by the European Medicines Agency but not yet reimbursed by most national health services.

The study will comprise the following clinical visits and timepoints:

- A baseline clinical visit (Visit 0 [V0] at Time 0 [T0]), within 14 days after screening
- A timepoint 12 weeks after baseline (T1); no clinic visit is required at that time
- A clinical visit at 6 months  $\pm$ 14 days (V1 or T2), and
- An optional clinical visit at 13 months  $\pm$ 4 weeks (V2 or T3)

Amyloid PET imaging (conducted at the local sites and read visually) will not be considered a separate clinical visit.

At T1, the investigator will review the result communicated by the managing physician (if the investigator and the managing physician are not the same person) and record the etiologic diagnosis made by the managing physician, rate the managing physician's diagnostic confidence (0% to 100%, visual analogue scale [VAS]) as well as the managing physician's estimate of the likelihood that the patient's symptoms are due to AD (0% to 100%, VAS), and record the effective date of the managing physician's etiologic diagnosis and management plan. This does not need to be a clinical visit.

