### 8.3.2 Randomisation

This is a phase 4, open label, randomised study.

Patients will be randomised in a 1:1:1 ratio into 1 of the following 3 groups:

- **Early Amyloid PET arm:** These participants will undergo amyloid PET imaging within 4 weeks after baseline. The results of the PET imaging must be communicated to the managing physician as soon as they are available. Amyloid PET will be carried out with high priority for early amyloid PET arm patients. For participants in this arm, an optional second amyloid PET scan will be performed 12 to 18 months ( $\pm 28$  days) after the initial scan.
- **Late Amyloid PET arm:** These patients will undergo amyloid PET imaging at 8 months  $\pm 8$  weeks after baseline.
- **Free Choice arm:** The managing physician will choose whether and when each participant will have amyloid PET imaging at any time between baseline and 12 months after baseline.

Randomization will be performed by using permuted blocks assuring equal numbers to all arms. Randomization will be stratified by centre and baseline syndromic diagnosis. Participants will be randomly assigned (1:1:1) to 1 of 3 arms and randomization will continue until 300 SCD plus, 300 MCI, and 300 dementia where AD is a differential diagnosis have been included.

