## **9.6 Amyloid PET for Late Amyloid PET Arm, 8 Months ( $\pm$ 8 Weeks After Baseline)**

All female participants of childbearing potential must have a negative pregnancy test before the imaging study is done. The participants in the Late Amyloid PET arm of the study will undergo amyloid PET imaging at 8 months ( $\pm$ 8 weeks) after baseline. Amyloid PET scan must take place after the T2 visit at 6 months  $\pm$  14 days.

If the managing physician chooses to order amyloid PET imaging for the participants in the Free Choice arm, those participants may undergo the imaging at any time from baseline to 12 months after baseline.

The following will be recorded for all participants who have undergone amyloid PET imaging:

- Review of current medications
- Amyloid PET scan results
- All AEs that occurred within 48 hours of study drug administration
- All SAEs occurring within 30 days of study drug administration

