### **12.5.3 Handling of missing values/censoring/discontinuations**

The reasons for incomplete data are many and include major protocol deviations, dropout because of study withdrawal or death, non-attendance at clinical visits, missing questionnaire items, uninterpretable images, etc.

The primary efficacy analysis will be conducted on the PPS population, which is based on complete cases.

Secondary efficacy analyses will be conducted on the FAS population. In time-to-event analyses, dropout and major protocol deviations are accounted for by censoring at the time of dropout or protocol deviation. In cross-sectional analyses and analyses of change between 2 timepoints, only complete cases will be included. Cases with a major protocol deviation before the first timepoint in the cross-sectional or change analysis will be excluded. The longitudinal mixed-effect analyses will be based on the observed cases. Data will be censored after a major protocol deviation. The underlying assumption in all analyses is that missing data are missing at random and not related to the primary outcome.

The proportion of missing data at each time point will be computed for the Early Amyloid PET, Late Amyloid PET, and Free Choice arms separately, and stratified for SCD Plus, MCI, and dementia.

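### The log-rank test of time to a communicated high-confidence diagnosis has no stated horizon, so as written it includes the period after the Late arm's own scan and can lose substantial power

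*Protocol*

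**What the plan says.** The synopsis lists as a secondary endpoint the difference between "the Early Amyloid PET arm and the Late Amyloid PET arm in the time (from baseline) to communicate" a diagnosis held with at least 90% confidence. Section 12.6.1.1 and the synopsis (Secondary Efficacy Analyses) both say that this difference "will be tested by the log-rank test", with Kaplan-Meier estimates of cumulative incidence. Neither place gives a horizon or a weighting.

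Section 12.5.3 supplies the censoring rule: "In time-to-event analyses, dropout and major protocol deviations are accounted for by censoring at the time of dropout or protocol deviation". It does not mention censoring at T1, at T2 or at the Late scan.

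The schedule is in section 8.3.2. For the Early arm: "These participants will undergo amyloid PET imaging within 4 weeks after baseline". For the Late arm: "These patients will undergo amyloid PET imaging at 8 months", with a window of 8 weeks either side. Section 9.6 adds, for the Late arm: "Amyloid PET scan must take place after the T2 visit at 6 months". Follow-up then continues to T3, which section 6.1.1 describes as "An optional clinical visit at 13 months".

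The hypothesis that this endpoint serves is in section 5.2: early PET "will enable an earlier etiologic diagnosis with high confidence vs the late adoption".

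**The concern.** The two arms differ in access to study PET only until the Late scan. After that, the Late arm receives the same test. If the scan is informative, the hazard of a confident diagnosis is higher in the Early arm during the first weeks and higher in the Late arm after its scan. The hazards cross because of the design.

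The unweighted log-rank statistic adds observed-minus-expected events over the whole time axis with equal weight. The later Late-arm diagnoses enter with the opposite sign and offset the early difference. For a given 12-week difference, the more of it the Late scan recovers, the larger the offset. At stake is power for the secondary endpoint that measures time to diagnosis directly: a real early advantage could be reported as non-significant because the comparator was later given the scan.

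**Working it through.** **1. The protocol's own power figures.** Section 12.7 gives more than 99%, 99.6%, 93% and 61% for 12-week differences of 25, 20, 15 and 10 points (300 per arm, 10% withdrawal), and 80% per stratum at 25 points. No power is stated for the time-to-diagnosis test. Take n = 300 × 0.9 = 270, two-sided 0.05, proportions centred on 0.5 (an assumption) and a continuity correction:

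power = Φ{[d − 1/n − z√(2p̄(1−p̄)/n)] / √[(p₁(1−p₁) + p₂(1−p₂))/n]}

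This gives 99.99%, 99.6%, 92.7% and 61.0%. With n = 90 and alpha 0.05/3 it gives 79.9% per stratum. All the stated figures reproduce. At 25 points this centring means 37.5% diagnosed in the Late arm and 62.5% in the Early arm.

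**2. Timing.** With 30.44 days per month, 8 months minus 8 weeks is 243.5 − 56 = 187.5 days (6.2 months), and plus 8 weeks is 299.5 days (9.8 months). Every scheduled Late scan falls after week 12 and before 13 months.

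**3. Hand calculation of the offset.** Take 300 per arm, no dropout, diagnoses spread evenly to week 12, a Late-arm week-12 proportion pL = 0.375 and d = 0.25. Full catch-up means that the Late scan gives each undiagnosed participant the chance d/(1 − pL) = 0.25/0.625 = 0.40 of a diagnosis. That is 187.5 × 0.40 = 75 further Late diagnoses.
- To week 12: Early observed 187.5, expected 187.5 − 75·ln 2 = 135.5. Difference +52.0, variance 73.9, Z = 52.0/√73.9 = 6.0.
- After the Late scan: Early observed 0, expected 112.5·ln(300/225) = 32.4. Difference −32.4, variance 18.3.
- Combined: 52.0 − 32.4 = 19.6, variance 92.2, Z = 19.6/√92.2 = 2.0. Approximate power is Φ(2.04 − 1.96) = 53%.

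At d = 0.15 the same steps give +29.9 (variance 67.2, Z = 3.6), then −20.9 (variance 11.2). Combined, 9.0/√78.4 = 1.0, so power is about 17%.

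**4. Simulation.** 300 per arm, 10% dropout, Late scan at 6.2–9.8 months, two-sided 0.05, no background diagnoses after week 12, 1,000 replicates per cell. Power of the log-rank test:

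| pL | d (points) | To 6 months | 13 months, full catch-up | 13 months, half catch-up | 13 months, full catch-up, half followed past 6 months |
|---|---|---|---|---|---|
| 0.2 | 25 | 100% | 34% | 97% | 96% |
| 0.375 | 25 | 100% | 50% | 98% | 97% |
| 0.5 | 25 | 100% | 74% | 98% | 99% |
| 0.6 | 25 | 100% | 93% | 100% | 100% |
| 0.2 | 15 | 98% | 12% | 65% | 60% |
| 0.375 | 15 | 93% | 17% | 61% | 62% |
| 0.5 | 15 | 94% | 25% | 64% | 63% |
| 0.6 | 15 | 94% | 37% | 74% | 72% |

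At pL = 0.375 and 25 points the mean Z falls from 5.85 to 2.01, in line with step 3. A second simulation on the same design inputs gave 38–81% at 25 points and 15–33% at 15 points for full catch-up with pL 0.2–0.5.

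**5. Other assumptions.** With background diagnoses at 0.03 per month after week 12 (pL 0.1–0.4) and full catch-up, 13-month power at 25 points is 40–68%. To T2 it is about 100% at 25 points and 92–99% at 15. With no catch-up, the two horizons give the same power.

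**The case against.** The strongest objection is that the horizon of a secondary time-to-event analysis is ordinary statistical analysis plan content. Section 12.1 promises such a plan, and a log-rank test cut at T2 would not contradict section 12.6.1.1. This stands in part: the 13-month horizon is inferred from the absence of a cut and from section 12.5.3, and the protocol nowhere states it. But the protocol does more than stay silent. It names the test and says when time-to-event data are censored, and those two statements together carry the analysis past the Late scan.

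A reader might infer that the Late arm's catch-up cancels the early benefit and removes most of the power. The documents do not support that as a general statement. At the protocol's own 25-point effect and pL = 0.375, about half the power is lost even with full catch-up, and almost none with half catch-up. T3 is optional, so many participants may not be observed to 13 months. Other investigations remain open to all participants, so the background diagnosis rate is unknown.

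A reader might also infer that the trial cannot show earlier diagnosis. That does not follow. The primary 12-week chi-squared test is completed before any scheduled Late scan, with more than 99% stated power at 25 points. The Kaplan-Meier curves would show early separation and later convergence. The log-rank test also keeps its type I error.

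**Conclusion.** The concern holds in conditional form. Read as written, the test covers a period in which the design reverses the hazard difference, so it is poorly matched to the hypothesis in section 5.2. The loss ranges from nothing (no catch-up) to most of the power (15 points with full catch-up, or 25 points with full catch-up and a low base rate). In between, for full catch-up, complete follow-up and pL of 0.2–0.5, power is roughly 35–80% at 25 points and 12–33% at 15 points, against about 100% and 93–98% to T2. With half catch-up, or half of participants followed past 6 months, a 25-point effect is still detected with about 96–100% power, but a 15-point effect with only 60–74%.

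Base rate, size of catch-up, background rate and T3 attendance are all assumptions. Full catch-up means only that the scan is as informative at month 8 as in the first month. The mechanism itself needs only the scan schedule and some catch-up.

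**What to change.** State in section 12.6.1.1 and in the synopsis that the formal log-rank comparison is administratively censored in both arms at one fixed day from baseline corresponding to T2. The end of the T2 window is one option (6 months plus 14 days, 182.6 + 14 = about day 197), so that diagnoses communicated at the T2 visit count. A fixed day, not the visit date, keeps the cut the same in both arms. The Late scan window opens at about day 188, so a Late participant with an early T2 visit could be scanned in the last nine days or so. Few diagnoses should be communicated in that gap, but it should be acknowledged when the day is chosen.

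Keep the Kaplan-Meier curves to 13 months as description. The difference in restricted mean time to 13 months is an optional supportive measure. In a simulation with 270 per arm, week-12 proportions symmetric about 50% and full catch-up, its power was 98% at 25 points and 64% at 15, against about 60% and 26% for the 13-month log-rank test.

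The cost is one sentence in two places, with no change to data collection. The downside is that events after the chosen day no longer enter the formal test.

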### **5.4.2.3 Health economics and patient-centred outcomes**

To assess the impact of amyloid PET imaging on:

- Patient-related outcomes (cognition, anxiety, depression, coping skills, and quality of life)
- Cost of diagnostic workup to the etiologic diagnosis with very high confidence ( $\geq 90\%$ )
- Number of patients who are discharged from the memory centre and the reason for discharge

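### Kaplan-Meier with death censored slightly overstates the cumulative incidence of communicated high-confidence diagnoses; Aalen-Johansen with death as a competing event would estimate it correctly

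*Protocol*

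**What the plan says.** The first-listed secondary endpoint (Protocol 10.1.2.1 and synopsis) is the time to communicate to the patient an etiologic diagnosis held with at least 90% confidence, Early versus Late Amyloid PET arm. Section 12.6.1.1 says the difference "will be tested by the log-rank test" and adds: "The cumulative incidence of diagnoses will be estimated with the Kaplan-Meier method". The synopsis, under Secondary Efficacy Analyses, repeats both.

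The censoring rule is in Section 12.5.3. Its reasons for incomplete data include "dropout because of study withdrawal or death". It then states: "In time-to-event analyses, dropout and major protocol deviations are accounted for by censoring at the time of dropout or protocol deviation". Read together, these two statements censor death. The same section adds: "The underlying assumption in all analyses is that missing data are missing at random and not related to the primary outcome". No competing-risk estimator is named.

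Discharge from the memory centre appears as an objective in Section 5.4.2.3 ("Number of patients who are discharged from the memory centre and the reason for discharge") and in the synopsis objectives. The endpoint and analysis lists (10.1.2.3, 12.6.1.3) count withdrawals instead, and no section says how discharge enters the time-to-event analysis.

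**The concern.** Censoring assumes that the event could still happen after the censoring time, at the rate seen in those still under observation. That is a usable assumption for someone who withdraws: the diagnosis may be made but is not seen. It cannot hold for someone who has died. The missing-at-random statement does not help here, because after death nothing is missing; the event has become impossible.

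1-KM therefore estimates the share who would be diagnosed if nobody died. The protocol names a different quantity, the cumulative incidence of diagnoses. Readers would take the curve as the share of memory-clinic patients told a confident diagnosis by a given time under each strategy, in a study that Section 4.1.1 says should inform cost-effectiveness. The population includes patients aged up to 85 and a planned 300 with dementia, so some deaths over 13 months are foreseeable.

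**Working it through.** The protocol states no figure for this endpoint, so there is none to reproduce. The size has to come from assumed rates.

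**Inputs**
- From the protocol: 300 patients per arm (12.7); last scheduled main-study time point 13 months (10.1.2); death censored (12.5.3); 1-KM as estimator (12.6.1.1).
- Assumed: 1-KM of 50%, 70% or 90% at 13 months, called K; probability of death by 13 months of 1% to 5% in the absence of a diagnosis, called D; constant hazards for both.

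**Formulas**

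Let a = -ln(1-K) and b = -ln(1-D). Under constant hazards the Aalen-Johansen incidence is

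AJ = a/(a+b) × [1 - (1-K)(1-D)],

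and the overstatement is K - AJ.

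**Worked example, K = 70%, D = 5%**
- a = 1.204, b = 0.0513, a/(a+b) = 0.9591
- 1 - 0.30 × 0.95 = 0.715
- AJ = 0.9591 × 0.715 = 0.6858
- Overstatement = 70.0% - 68.6% = 1.4 points
- Share of the arm dying undiagnosed = 0.715 - 0.6858 = 2.9%. Deaths after diagnosis do not matter here.

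**Overstatement in one arm at 13 months (percentage points)**

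| Assumed mortality D | K = 50% | K = 70% | K = 90% |
|---|---|---|---|
| 1% | 0.22 | 0.28 | 0.29 |
| 2% | 0.44 | 0.57 | 0.58 |
| 3% | 0.67 | 0.85 | 0.88 |
| 5% | 1.12 | 1.42 | 1.47 |

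For scale, the binomial standard error with 300 patients, sqrt(K(1-K)/300), is 2.9, 2.6 and 1.7 points for the three columns. At 5% mortality the bias is therefore about 0.4, 0.5 and 0.8 standard errors.

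At week 12, with K between 30% and 70% and assumed mortality of 0.5% to 1%, the same formula gives 0.07 to 0.28 points.

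**Effect on the Early-minus-Late gap, equal mortality in both arms**
- 70% versus 50%, D = 5%: displayed gap 20.0 points; Aalen-Johansen gap 68.58 - 48.88 = 19.7 points; inflation 1.42 - 1.12 = 0.3 points.
- 70% versus 50%, D = 1%: 0.28 - 0.22 = 0.06 points.
- 90% versus 50%, D = 5%: 1.47 - 1.12 = 0.35 points.

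**What does not change**
- A log-rank test that censors deaths remains a valid comparison of the cause-specific diagnosis hazards.
- The primary analysis is a chi-squared test of week-12 proportions (12.5.2) and does not use the curve.

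**The case against.** Three arguments deserve weight.

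*Little depends on the curve.* It describes one secondary endpoint, and no test, decision or sample size changes. Section 7.4 also excludes patients with life-threatening unstable disease, and Section 7.3 requires that patients can complete the visits, so deaths should be few. This stands and sets the size of the point.

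*The statistical analysis plan could settle it.* Section 12.1 promises one, and it is not at hand. But the protocol does not leave the estimator open: it names Kaplan-Meier, and the censoring rule that goes with it is also fixed.

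*The problem could be argued to be larger.* A reader might infer that discharge without a diagnosis also prevents the event, or that the 10% withdrawal assumed in Section 12.7 measures competing exits. If 10% to 20% left by events that truly ruled out a diagnosis, the same formula would give about 2.3 to 6.1 points. The document does not support that reading:
- Discharge is only an objective. No section says that it ends participation or is censored. The week-12 assessment needs no clinic visit, and Sections 9.4 and 9.5 record assessments for all participants at week 12 and month 6, so a discharged patient may still receive a study diagnosis.
- The 10% covers withdrawal without a stated cause. Ordinary withdrawal leaves a diagnosis unobserved, not impossible, and censoring it is standard if it is non-informative.

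A reader might also infer that the bias materially inflates the difference between arms. Under equal mortality it does not, as the gap figures show.

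**Conclusion.** The point holds for death. The protocol labels the quantity cumulative incidence, fixes an estimator that does not estimate it when deaths occur, and states a rule that censors death. The direction is certain: the curve is too high whenever someone dies undiagnosed.

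The size is about 0.2 to 1.5 points per arm at 13 months. This rests on assumed mortality of 1% to 5%, 1-KM of 50% to 90%, and constant hazards; the protocol supplies none of these rates. It is a small, well-defined error in a descriptive secondary estimate. How discharge without a high-confidence diagnosis is handled is undefined, which is a matter to clarify and not a demonstrated bias.

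**What to change.** - In Section 12.6.1.1 and the matching synopsis bullet, replace Kaplan-Meier with the Aalen-Johansen estimator in each arm, with death before a communicated high-confidence diagnosis as the competing event.
- In Section 12.5.3, take death out of the dropout that is censored for this cumulative-incidence estimate. Keep censoring for withdrawal, loss to follow-up and end of study.
- Keep the log-rank test, described as a comparison of cause-specific hazards.
- State how discharge without a high-confidence diagnosis is handled. Treat it as competing only if the sponsor confirms that it ends the possibility of a study diagnosis and that its date is captured. Table 1 has no discharge item, so the second condition needs checking.

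The cost for death is one changed estimator and a date of death for each patient who dies. The reported incidence becomes slightly lower. If nobody dies undiagnosed, Aalen-Johansen equals 1-KM and nothing changes. Adding discharge could require a new data item, so it should not be promised before that is settled.

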## 6 STUDY DESIGN

### 6.1 Overall Study Design and Plan

#### 6.1.1 Study design

This is a phase 4 multicentre, open-label study of amyloid PET imaging of participants who have one of the following syndromic diagnoses: SCD-plus, MCI, or dementia where AD is in the differential diagnosis. Participants will be randomised to 3 arms. Arms 1 and 2 allow testing the impact of amyloid PET on diagnostic confidence, patient management, and ultimately decision making and the cost-effectiveness of dementia care. Arm 3 allows to investigate the optimal timing of amyloid PET imaging in the diagnostic workup.

The baseline visit must take place within 14 days after the screening visit and can be combined with the screening visit. At baseline, the investigator will record the syndromic diagnosis made by the managing physician, the managing physician's confidence in that diagnosis, and the managing physician's estimate of the likelihood that the patient's symptoms are due to AD. (According to [\[Johnson et al, 2013\]](#), the managing physician is a dementia expert trained and board-certified in neurology, psychiatry, or geriatric medicine who devotes a substantial proportion [at least 25%] of patient contact time to the evaluation and care of adult acquired cognitive impairment or dementia.). The investigator and the managing physician may be but do not have to be the same person. Participants will be stratified by syndromic diagnosis (SCD-plus, MCI, or dementia) and then randomly assigned (1:1:1) to 1 of 3 arms:

- **Early Amyloid PET Arm:** Participants will undergo amyloid PET imaging within 4 weeks after the baseline visit. Amyloid PET will be carried out with high priority over other diagnostic exams except MRI in the early amyloid PET arm. The results of the scan must be communicated to the managing physician as soon as available. Early Amyloid PET arm participants will undergo an optional second amyloid PET scan within at 12 to 18 months window after the initial scan.
- **Late Amyloid PET Arm:** Participants will undergo amyloid PET imaging at 8 months ( $\pm 8$  weeks) after baseline.
- **Free Choice Arm:** The managing physician will decide whether the participant undergoes amyloid PET imaging. The imaging can be done at any time within 12 months after baseline. The reason for the choice will be collected.

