## **12.6 Secondary Analyses**

### **12.6.1 Secondary efficacy variables**

In the analyses of the secondary efficacy variables, a cross-sectional difference between arms in a secondary endpoint at T1, T2, T3, or T4 (see Table 1) will be carried out by a chi-squared test if the endpoint is dichotomous, a 2-sided *t*-test if the endpoint is normal, and Mann-Whitney test if the endpoint is categorical or continuous and non-normal. The effect of baseline characteristics such as age, gender, MMSE, etc will be studied by a linear or logistic regression model.

A difference between study arms in the longitudinal change of a secondary endpoint will be tested by means of logistic or linear regression where the first measurement is a covariate (ANCOVA analysis) and the second measurement is the outcome. Differences in longitudinal

trends between arms will also be examined by means of the mixed-effects regression model. The effects of baseline characteristics such as age, gender, MMSE, etc. will be studied by including them in the regression models.

All tests will be 2-sided and the significance level will be set at 5%. Bonferroni corrections for multiple testing will be applied when appropriate. Point estimates will be presented together with 95% Wald confidence intervals. A 95% non-parametric confidence interval will be constructed if the estimate is non-normal.

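### The Free Choice calendar-time test names no stratification by syndrome, so if strata fill unevenly and PET use differs by syndrome, a shift in patient mix can be read as a change in PET placement

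*Protocol*

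**What the plan says.** Protocol 12.6.1.1 fixes both the grouping and the test for the Free Choice arm: "The Free Choice arm will be divided into 3 equal-sized groups, according to the date of randomisation", and then "a change in the placement of amyloid PET imaging over time in the diagnostic workup will be tested by a log-rank test". The synopsis repeats this under its secondary efficacy analyses. No stratification factor or covariate is named for the test in either place.

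On recruitment, 8.3.2 says "Randomization will be stratified by centre and baseline syndromic diagnosis" and that "randomization will continue until 300 SCD plus, 300 MCI, and 300 dementia where AD is a differential diagnosis have been included". Section 6.1.1 sets the sizes: "The goal will be to enrol 100 participants per stratum in each arm, for a total of 900 participants". The Free Choice arm is therefore about 300 patients, 100 per syndrome, and each date-third about 100. PET timing in this arm is open: "The imaging can be done at any time within 12 months after baseline".

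The covariate provision in 12.6.1 reads "The effect of baseline characteristics such as age, gender, MMSE, etc will be studied by a linear or logistic regression model". A similar provision covers the change and mixed-effects models. Neither reaches a log-rank test.

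**The concern.** The other log-rank test in 12.6.1.1, Early against Late, compares randomised groups, so patient mix is balanced by design. Thirds by randomisation date have no such protection. Their composition depends on who was still being recruited.

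The stratum caps make a change in composition possible. Once the fastest-filling syndrome reaches its cap, later entrants come only from the others. If managing physicians order PET more or less often, or sooner or later, in SCD-plus than in dementia, the last third will show a different time-to-PET curve even though nobody's practice has changed.

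Change in PET placement is a named secondary objective (5.4.2.1), and this is the only test specified for it. A significant result would naturally be reported as physicians changing how they use amyloid PET.

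**Working it through.** **The plan's own figure.** There is none for this test. The power figures in 12.7 concern the primary analysis only.

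**Inputs from the protocol.** 300 Free Choice patients, 100 per syndrome (6.1.1); each stratum closes when full (8.3.2); three equal groups by entry order and a log-rank test (12.6.1.1); 12-month window for PET (6.1.1); two-sided 5% level (12.6.1).

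**Assumed inputs.** Relative accrual by stratum and 12-month PET uptake by stratum, both in the order SCD-plus, MCI, dementia. In the main scenarios the slowest-filling stratum also has the lowest uptake.

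**Step 1: mix per third.** With accrual 1:1.5:2 the shares are 1/4.5 = 22%, 1.5/4.5 = 33% and 2/4.5 = 44%. After 200 patients the strata hold about 44, 67 and 89, so none has closed and thirds 1 and 2 share the same expected mix. The last third takes what is left: 100 − 44 = 56, 100 − 67 = 33 and 100 − 89 = 11. With accrual 1:1.25:1.5 the shares are 27/33/40%, and the last third is 47/33/20.

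**Step 2: the apparent change.** Take accrual 1:1.5:2 and uptake 40/60/80%, constant over time in every syndrome.

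- Thirds 1 and 2: 0.222×40 + 0.333×60 + 0.444×80 = 64.4%.
- Third 3: 0.556×40 + 0.333×60 + 0.111×80 = 51.1%.

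Uptake appears to fall by 13.3 points with no change in practice. With uptake 50/60/70% the figures are 62.2% and 55.6%, a fall of about 6.7 points.

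**Step 3: false-positive rate.** Simulation with 1,000 arms per scenario. Time to PET is exponential with monthly hazard −ln(1 − uptake)/12 (for example −ln(0.4)/12 = 0.076 at 60%), censored at 12 months, with no dropout and no calendar effect within any syndrome. The three-group log-rank statistic (2 df) was computed pooled, and again with observed-minus-expected counts formed within syndrome and then summed. The simulation standard error near 5% is √(0.05×0.95/1000) = 0.7 points.

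| Accrual | Uptake (%) | Unstratified | Stratified by syndrome |
|---|---|---|---|
| 1:1:1 | 50/60/70 | 4.8% | 4.9% |
| 1:1:1 | 40/60/80 | 6.7% | 5.3% |
| 1:1.25:1.5 | 50/60/70 | 10.2% | 4.4% |
| 1:1.25:1.5 | 40/60/80 | 25.3% | 5.1% |
| 1:1.5:2 | 60/60/60 | 6.3% | 6.0% |
| 1:1.5:2 | 50/60/70 | 16.6% | 5.0% |
| 1:1.5:2 | 40/60/80 | 52.6% | 4.2% |
| 1:2:3 | 60/60/60 | 6.1% | 6.5% |
| 1:2:3 | 50/60/70 | 28.2% | 6.1% |
| 1:2:3 | 40/60/80 | 82.5% | 5.0% |

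Over all scenarios run, the unstratified test gave 4.8% to 6.7% with equal accrual, 4.2% to 6.3% with equal uptake at any accrual, and 4.7% to 6.2% when only MCI differed in uptake (60/70/60%) and accrual was unequal. The stratified test stayed between 4.2% and 6.5% throughout.

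**The case against.** **The inflation rests on assumptions.** This stands, and it limits the claim. A reader might infer that a shift in mix is bound to be mistaken for a change in placement. The protocol does not support that. It takes both unequal filling and syndrome-dependent PET use, and the protocol gives no figures for either. The caps alone create no shift. Both conditions are plausible: 7.3 and 7.5 set different entry criteria by syndrome, and 4.1.1 itself asks for whom amyloid PET is appropriate and when. Plausible is not established.

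**The last third need not be mostly the slowest stratum.** Also right. At 1:1.25:1.5 that stratum is 47% of the last third, and the first two thirds have the same expected mix. The test is still inflated there, to 10.2% or 25.3%.

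**Strata for a secondary log-rank test belong in the SAP.** This stands in part. Section 12.1 leaves further detail to an SAP that is not at hand, and nothing in the protocol forbids stratification. But the protocol did not leave this analysis open: it prescribes both grouping and test, and 12.11 requires departures from its analyses to be explained in the final report.

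**Two further criticisms do not hold.** A reader might add that staggered centre opening confounds the test in the same way. The protocol describes no such staggering, and it was not simulated. Stratifying jointly by centre and syndrome would also be thin: with at least 8 centres (synopsis), 300/(8×3) = 12.5 patients per cell at most, about 4 per third. A reader might also fault the 2-df test for ignoring the order of the thirds. The protocol states no monotone hypothesis, so an omnibus test is legitimate and a trend test is a preference.

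**Conclusion.** The concern holds in conditional form. As written, the test has no protection against drift in syndrome mix across non-randomised date groups. If strata fill unevenly and PET use differs by syndrome, it can report a calendar change that did not occur. In the scenarios that combine accrual of 1:1.25:1.5 to 1:2:3 with uptake of 50/60/70% to 40/60/80%, the false-positive rate is about 10% to 82% against a nominal 5%. If either condition is absent, it stays near 5%. These rates depend on assumed accrual and uptake, exponential times and no dropout. They show a possible range and do not predict this trial's error rate.

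The point affects one secondary endpoint in one arm. It does not touch the primary comparison or any Early-against-Late analysis.

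**What to change.** In the synopsis and in 12.6.1.1, specify that the three date-of-randomisation groups are compared by a log-rank test stratified by baseline syndromic diagnosis. A Cox model for time to PET, stratified by syndromic diagnosis and with date-third as a factor, would serve equally well. Report the number of SCD-plus, MCI and dementia patients in each third beside the result. Adjustment for centre and a trend test can be listed as optional sensitivity analyses.

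The cost is one sentence and one small table. No new data are needed, because syndromic diagnosis is recorded before randomisation and is already a randomisation factor. Where accrual is very uneven, a stratum nearly absent from the last third adds little to the comparison with that third: at 1:2:3 the fastest stratum has about 3 patients there. If the SAP already specifies this stratification, only the protocol wording needs aligning.
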